**DATA MONITORING**

**Interim analyses and the role of the Data Monitoring Committee**

The Trial Steering Committee will appoint an independent Data Monitoring Committee consisting of a Chairman, statistician and a clinician.

During the study, the Data Safety Monitoring Committee will be informed of any serious adverse events. The trial statistician will prepare unblinded data for examination by the Data Monitoring Committee when information from the first 200 patients becomes available and again when 400 patients have been analysed.  In the light of these analyses and the results of any other new relevant information, the Data Monitoring Committee will advise the Steering Committee if, in their view, the randomised comparisons have provided both; (i) "proof beyond reasonable doubt" that any of the study treatments is clearly indicated or clearly contraindicated in terms of a net difference in severe adverse reactions, and (ii) evidence that might be reasonably expected to influence the management of many clinicians.  In general a difference of at least 3 standard deviations (i.e. P<0.001) in an interim analysis of a major endpoint would be needed to justify halting, or modifying, the study prematurely, especially if the comparison were based on relatively few events (e.g. under 100). If this criterion is adopted, it has the
practical advantage that the exact number of interim analyses would be of little importance.

Unless this happens, the Steering Committee, investigators, and the coordinating centre staff (except those who supply the confidential analyses) will remain ignorant of the interim results on adverse reactions until the study is terminated. During the study, investigators and all others associated with the study may write to the chairman of the Data Monitoring Committee, drawing attention to any worries they may have about the possibility of particular adverse effects, or about any other matters that may be relevant.

The trial statistician will monitor recruitment to the trial, protocol adherence, and serious adverse events. The TSC will consider reports made by the trial statistician and any other relevant studies published during the timeframe of this trial. Recommendations made by the TSC will be passed by its Chairman to the attending clinicians in the three trial centres.

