**Expected start date : February 2005**

**Expected trial duration : 30-36 months**

**SYNOPSIS**

| **Title** | **Low dose adrenaline, promethazine, & hydrocortisone (alone and in combination) to prevent acute adverse reactions to antivenom in people bitten by snakes: randomised, double-blind, placebo-controlled trial** |
| --- | --- |
| Aim | Investigation of the efficacy and safety of pretreatment with adrenaline, promethazine & hydrocortisone (alone and in combination) in comparison with placebo to prevent acute adverse reactions to antivenom |
| Design | Type: a randomised, double-blind, placebo-controlled study  Number of centres: three  Estimated duration: six months – one year  Design: factorial 2x2x2 design |
| Sample size | At least 1000 patients are required to have 80% power at p<0.01 to detect a 25% reduction in the rate of acute adverse reactions to antivenom |
| Indication | Snakebite with evidence of systemic / severe local envenomation |
| Patient selection I | Inclusion criteria   - Age above 12 yrs - Patients admitted to hospital after snakebite in whom antivenom is indicated - Patients who give informed consent |
| Patient selection II | Exclusion criteria   - Patients in whom adrenaline may be contraindicated - Patients currently taking beta- or alpha-adrenoceptor antagonists, and tricyclic antidepressants - Pregnant and nursing women |
| Trial medication | Drugs: adrenaline, promethazine, & hydrocortisone alone and in combination  Placebo: 0.9% NaCl  Duration of treatment: once as pretreatment before antivenom |
| Efficacy variables | Efficacy:   - Reduction in acute adverse reactions to antivenom   Safety:   - Adverse reactions to trial medications |

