Several methods have been used to reduce acute adverse reactions to antivenom. A small test dose of antivenom to detect patients who may develop acute adverse reactions to the antivenom has no predictive value, can itself give rise to anaphylaxis, and is no longer recommended [Malasit et al., 1986]. Prophylactic use of hydrocortisone and antihistamines before infusion with antivenom is also practised widely, although the theoretical basis for their use is unclear. Antihistamines counter only the effects of histamine after its release and do not prevent further release, and one small randomised controlled trial demonstrated no benefit from the routine use of antihistamines [Fan et al., 1999]. Hydrocortisone takes time to act and may be ineffective as a prophylactic against acute adverse reactions that can develop almost immediately after antivenom treatment, which is very often administered urgently to snakebite victims. A recent study suggests that intravenous hydrocortisone is ineffective in preventing acute adverse reactions to antivenom, but if given together with intravenous chlorpheniramine (an antihistamine) it may reduce these reactions [Gawarammana et al., 2004]. However, this trial recruited only 52 patients and was not designed to study the efficacy of chlorpheniramine alone, making clear interpretation of the results and recommendations on pretreatment with steroids and antihistamines to prevent acute reactions to antivenom difficult.

In one study of 105 patients low-dose adrenaline given subcutaneously immediately before administration of antivenom to snakebite victims significantly reduced the incidence of acute adverse reactions to the serum [Premawardena et al., 1999]. However, the authors were unable to enrol sufficient participants to adequately establish safety, a major concern regarding the use of adrenaline in a prophylactic role [Khanna & Hawkins, 1999], particularly the risk of intra-cerebral haemorrhage [Dassanayake et al., 2002; Horowitz et al. 1996]. Therefore, further studies on the safety of this treatment are required before it can be recommended routinely.

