**Sample size and predicted events**

We estimate that acute adverse reactions occur in about 40% of patients who receive antivenom. Therefore, proportional reductions of 25-40% of acute adverse reactions would correspond to substantial absolute benefits (see Table). For an anticipated 25% reduction in adverse reactions from the current reaction rate by any one treatment with 80% power at p<0.01 using the proposed design, a sample size of 1000 would be needed for this study.

During the trial it is intended that blinded event rates (i.e. active and placebo groups combined) will be monitored and, if they are substantially lower than anticipated, the TSC will have the option of increasing the sample size.

**Table: Statistical power to detect 25-40% proportional reductions in acute adverse reactions to antivenom among 1000 randomised patients (based on 40% control group event rate)**

| **Proportional**  **reduction** | **Control group**  **500** | **Treatment group**  **500** | **Power for a type I error <0.01** | **Power for a type I error <0.05** | **Events avoided per 1000 treated** |
| --- | --- | --- | --- | --- | --- |
| 40% | 200 | 120 | >95% | >99% | 80 |
| 30% | 200 | 140 | 95% | >95% | 60 |
| 25% | 200 | 150 | 80% | >90% | 50 |

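### The last scheduled comparison by arm is at 400 of at least 1000 patients, so 60% or more of the trial runs with no planned by-arm review of rates

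*Protocol*

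**What the plan says.** The protocol's section on interim analyses and the role of the DMC schedules unblinded data "when information from the first 200 patients becomes available and again when 400 patients have been analysed". It names no later look. In general, it requires a difference of at least 3 standard deviations, glossed as P<0.001, in an interim analysis of a major endpoint before the trial is halted or modified. It adds that this criterion has the "practical advantage that the exact number of interim analyses would be of little importance".

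The synopsis sets the size as a minimum: "At least 1000 patients are required to have 80% power at p<0.01 to detect a 25% reduction". Under Sample size and predicted events, pooled blinded event rates are monitored and, if they run low, "the TSC will have the option of increasing the sample size".

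Other safety routes run for the whole trial. Under Adverse events, confirmed serious event reports go promptly and unblinded to the DMC chairman. Non-serious effects of the trial drugs are exempt from that route. The interim-analysis section also lets anyone associated with the study write to the chairman.

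The Background says of an earlier adrenaline trial of 105 patients that "the authors were unable to enrol sufficient participants to adequately establish safety, a major concern regarding the use of adrenaline in a prophylactic role".

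**The concern.** Safety of the pretreatments is a stated objective, and the Background presents it as the unresolved question for adrenaline. The scheduled by-arm comparisons nevertheless all fall in the first 40% of recruitment, when a difference in rates is hardest to see. After patient 400 the DMC is due to receive single cases, not rates by arm.

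Single cases are a weak guide here. The features that define a severe reaction (low blood pressure, cyanosis, confusion, altered consciousness) can come from the antivenom or the bite as well as from a trial drug. A drug effect would therefore show mainly in a comparison of rates. Some specified reactions to study treatments, such as a blood-pressure rise or ECG changes, may not count as serious and then need not reach the DMC promptly.

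If a drug did raise severe reactions, and this became clear only after patient 400, no scheduled review would show it before the final analysis.

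**Working it through.** **Inputs from the protocol.** N = 1000, as a minimum; 500 v 500 for each drug margin; looks at 200 and 400; guide of 3 SD or P<0.001; two-sided P values. The planning rate is for any acute reaction: "We estimate that acute adverse reactions occur in about 40% of patients who receive antivenom". **Assumed, because the protocol gives none:** the severe-reaction rates used below.

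**1. The plan's own figures.** The protocol claims 80% power for 40% v 30% at p<0.01 with 500 per margin. With a pooled two-sided test, power = Φ[(0.10 − 2.576 × √(2 × 0.35 × 0.65/500)) / √((0.24 + 0.21)/500)] = Φ[(0.10 − 0.0777)/0.0300] = Φ(0.743) = 77%. The stated 80% is not quite reproduced, but this does not affect the present point, which uses only the planned 1000.

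The two forms of the guide also differ. Two-sided, 3 SD is P = 0.0027, while P<0.001 needs 3.29 SD. Both are carried through below.

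**2. Patients after the last scheduled comparison.** 1000 − 400 = 600; 600/1000 = 60%. With half allocated to each drug, 600/2 = 300 per drug.

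**3. Single-look chance of crossing 3 SD**, with n patients per side: Φ[(|p₁ − p₀| − 3√(2p̄(1 − p̄)/n)) / √((p₁(1 − p₁) + p₀(1 − p₀))/n)]. For 40% v 30% at 400 patients (n = 200): Φ[(0.10 − 0.1431)/0.0474] = Φ(−0.909) = 18%.

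| Rates | 200 | 400 | 600 | 800 |
|---|---|---|---|---|
| 40% v 30% (design effect, any reaction) | 6% | 18% | 33% | 49% |
| 20% v 10% (assumed) | 15% | 42% | 67% | 83% |
| 3% v 1% (assumed) | 2% | 6% | 11% | 16% |

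**4. Chance of crossing at any look before the end**, by simulation with pooled z-tests on margins of N/2:

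| Assumed severe rates | Guide | Looks at 200, 400 | Looks at 200, 400, 600, 800 |
|---|---|---|---|
| 24% v 12% | P<0.001 | 45% | 89% |
| 24% v 12% | 3 SD | 57% | 94% |
| 24% v 16% | P<0.001 | 10% | 36% |
| 24% v 16% | 3 SD | 17% | 47% |

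As a hand check of the first row, the single-look chance at P<0.001 is Φ[(0.12 − 3.29 × 0.0384)/0.0379] = Φ(−0.17) = 43% at 400 patients, and Φ[(0.12 − 3.29 × 0.0272)/0.0268] = Φ(1.14) = 87% at 800. Both sit just below the cumulative figures, as they should.

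**5. Cost in error, per drug, with no drug effect (16% in both groups).**

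| Quantity | Guide | Two looks | Four looks |
|---|---|---|---|
| False early crossing | P<0.001 | 0.2% | 0.3% |
| False early crossing | 3 SD | 0.5% | 0.8% |
| Overall error, final test at 0.01 | P<0.001 | 1.1% | 1.15% |
| Overall error, final test at 0.01 | 3 SD | 1.4% | 1.5% |

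With a final test at 0.05, overall error is about 5.1% under P<0.001 and 5.3% under 3 SD, whether there are two looks or four.

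**The case against.** The strongest reply is that monitoring does not stop at patient 400. Serious adverse events reach the DMC chairman unblinded throughout, the trial statistician follows them, and anyone may write in with a worry. The guide holds only in general, the committee may weigh other new information, and nothing forbids it from asking for further tabulations. The remark that the number of looks matters little even suggests that the number was meant to stay open. All of this stands.

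It rules out three stronger readings that a reader might infer. The first is that the DMC sees nothing unblinded after 400; the serious-event reports contradict that. The second is that no review could stop the trial after 400; the documents put no such bar on the committee. The third concerns a harm absent in controls. It would need 11 v 0 events for Fisher P<0.001, and a true 3% harm reaches 11 events with 4% chance by patient 400 and 66% by patient 800. Those are chances of crossing a formal guide, not of being noticed. A serious harm such as intracerebral haemorrhage would already have been reported case by case.

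The reply also notes, rightly, that the event rates are assumed, that the error cost depends on which form of the guide is used, and that early looks with continuous case reporting are a design choice and not a contradiction.

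What it does not supply is a scheduled comparison of rates by arm after 400, or any prompt route for non-serious specified reactions. The blinded monitoring pools the arms, so it cannot show a difference between them. Investigators who may write to the chairman are themselves blinded.

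**Conclusion.** The point holds as a gap in a schedule that the protocol itself fixes. At least 600 of 1000 patients, about 300 per drug, are treated after the last scheduled by-arm comparison. Both planned looks come where the guide has little chance of being crossed: 18% at best for the design effect on any reaction. For the larger assumed differences in severe reactions, two more looks raise the chance of crossing before the end from 45% to 89%, or from 10% to 36%, at P<0.001. The 3 SD form leads to the same conclusion.

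These gains depend on the assumed rates and on equal margins. They would be small for rare harms: at 3% v 1% a single look at 800 crosses 3 SD only 16% of the time, so for such harms the tabulated rates matter more than the guide. Since the plan says that its criterion makes the number of analyses unimportant, it offers no statistical reason to end the scheduled looks at 40%. This is a cheap improvement, not an error that invalidates the trial.

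**What to change.** In the section on interim analyses and the role of the DMC, schedule unblinded reports to the existing committee at 600 and 800 patients as well as at 200 and 400, and at every further 200 if the sample size is increased, under the same guide. Each report should show severe reactions, deaths and the specified adverse reactions to study treatments, by each drug margin, so that non-serious specified reactions are also compared. The two forms of the guide (3 SD and P<0.001) should be reconciled in the same edit.

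The cost is two more reports by the existing trial statistician, with no extra patients or procedures. The chance of a false early crossing rises by about 0.1 percentage points per drug at P<0.001, or about 0.3 at 3 SD. The longest stretch without a scheduled comparison falls from 600 patients to 200.

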**DATA ANALYSIS**

# Methods of analysis

The fundamental assessments of efficacy will involve comparisons of the proportions of patients experiencing an event among all the randomised patients in their originally allocated treatment group, irrespective of what treatment they were actually given (i.e. “intention-to-treat” analyses). Two-sided P values will be used. No allowance will be made for multiple hypothesis testing in the primary comparison of each of the three study treatments in this 2 x 2 x 2 factorial study. For secondary and, particularly, for tertiary comparisons, allowance will be made for multiple hypothesis testing, taking into account the nature of the events (including timing, duration, and severity) and evidence from other studies.

The independent effects and effects of interactions of the three interventions will be assessed by using Cox regression. Cox regression will be used with a constant time to event for all subjects as we are only interested in reaction rate and not in the time to reaction.

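### The interim stopping guide treats 3 standard deviations and P<0.001 as the same boundary, but 3 SD is two-sided P=0.0027 and two-sided P<0.001 needs 3.29 SD

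*Protocol*

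**What the plan says.** The guide is in the Protocol under Data Monitoring, in the section on interim analyses and the role of the Data Monitoring Committee: "In general a difference of at least 3 standard deviations (i.e. P<0.001) in an interim analysis of a major endpoint would be needed" to support ending or altering the trial early. The protocol asks for extra caution when events are few. It adds that, with this criterion, the exact number of interim looks hardly matters.

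Unblinded data go to the committee "when information from the first 200 patients becomes available and again when 400 patients have been analysed". The committee judges whether "any of the study treatments is clearly indicated or clearly contraindicated in terms of a net difference in severe adverse reactions", so the guide works in both directions.

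Sidedness is not restated in that section. Methods of analysis says: "Two-sided P values will be used". No one-sided convention appears anywhere in the protocol.

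For scale, the section on sample size and predicted events plans the trial "with 80% power at p<0.01 using the proposed design" and concludes that "a sample size of 1000 would be needed for this study". Its power table also gives a 0.05 column.

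**The concern.** The sentence presents the P value as a restatement of the SD figure. If the two differ, the protocol gives two boundaries and does not say which one applies. A committee looking at a result between them could cite the same sentence for stopping or for continuing. This is the only numerical stopping guide in the protocol. Its strictness also determines how far the remark about the number of looks is true, because a looser boundary uses up more type I error at each look.

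**Working it through.** **Inputs.** From the interim section: boundary of 3 SD, also given as P<0.001; looks at 200 and 400 patients. From the sample size section: total 1000, level 0.01 (0.05 also tabulated), reaction rate 40%. From Methods of analysis: two-sided P values. I read a difference of 3 SD as a z statistic of 3.

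**Step 1: try to reproduce P<0.001 from 3 SD.** Two-sided P = 2 × (1 − Φ(z)); one-sided P = 1 − Φ(z).

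| Reading of 3 SD | One-sided P | Two-sided P |
| --- | --- | --- |
| Normal | 0.00135 | 0.0027 |
| t, 198 df | 0.0015 | 0.0030 |
| t, 398 df | 0.0014 | 0.0029 |

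No variant falls below 0.001, so the stated figure is not reproduced.

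**Step 2: the reverse direction.** Two-sided P=0.001 gives z = Φ⁻¹(0.9995) = 3.29. One-sided P=0.001 gives z = Φ⁻¹(0.999) = 3.09. On the two-sided reading the forms differ by 3.29 − 3.00 = 0.29 SD, or 0.0027/0.001 = 2.7-fold in P.

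**Step 3: data that fall between the two forms.** Pooled z = (p1 − p2) / √(p̄(1 − p̄) × 2/n), with n patients in each half of a factorial comparison. I assume equal halves and a 40% control rate.

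- 200 patients, 40/100 v 20/100: p̄ = 0.30, z = 0.20/√(0.30 × 0.70 × 0.02) = 3.09, P=0.0020. Meets 3 SD, fails P<0.001.
- 200 patients, 40/100 v 18/100: z = 3.43, P=0.0006. Meets both.
- 400 patients, 80/200 v 51/200: p̄ = 0.3275, z = 0.145/√(0.3275 × 0.6725 × 0.01) = 3.09, P=0.0020. Meets 3 SD, fails P<0.001.
- 400 patients, 80/200 v 49/200: z = 3.32, P=0.0009. Meets both.

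The 40% is the protocol's rate for reactions of any kind. The primary outcome is severe reactions, for which no rate is given, so these counts are illustrations only.

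**Step 4: effect on type I error.** Information fractions are 200/1000 = 0.2, 400/1000 = 0.4, and 1.0. Crossing probabilities under no effect come from numerical recursion over the looks. Every crossing is counted as a stop, and the final test is unadjusted.

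| Final level | Boundary | Look 1 | Look 2 | Final | Total per comparison |
| --- | --- | --- | --- | --- | --- |
| 0.01 | 3 SD | 0.0027 | 0.0022 | 0.0091 | 0.0141 |
| 0.01 | P<0.001 | 0.0010 | 0.0009 | 0.0096 | 0.0114 |
| 0.05 | 3 SD | 0.0027 | 0.0022 | 0.0480 | 0.0529 |
| 0.05 | P<0.001 | 0.0010 | 0.0009 | 0.0491 | 0.0510 |

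The excess over the nominal level at 0.01 is 0.0041 with 3 SD and 0.0014 with P<0.001. At 0.05 it is 0.0029 and 0.0010.

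**The case against.** The strongest reply is that this is guidance, not a binding boundary. The committee advises the Steering Committee. It must be persuaded both that the evidence is beyond reasonable doubt and that it would change the practice of many clinicians, and it also weighs new outside information. The numerical sentence is worded as a general guide, says what is necessary rather than what is sufficient, and is followed by a sentence that makes its adoption conditional. A committee could properly advise either way at z=3.1 or at z=4, and correcting the figures would not remove that discretion. Both forms are also strict for an early look.

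All of this stands, and it limits the size of the point. It does not make the two figures equal, and a guide is still easier to apply if it states one number.

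A reader might go further and infer that the guide sets the same extreme hurdle for rare harms of the study drugs, intracerebral haemorrhage in particular. The documents do not support this. The guide concerns a major endpoint, and contraindication is judged by a net difference in severe adverse reactions. Severe reactions to antivenom are the primary outcome, while haemorrhage is listed separately among the specified adverse reactions to study treatments. Serious adverse events also have their own route: under Adverse events they are reviewed at once, and confirmed reports go unblinded to the committee's chairman with no P threshold. A separate, less extreme boundary for harm would be a design preference, not the correction of an error.

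**Conclusion.** The point holds as an arithmetic error in the stopping guide. The false equivalence does not depend on sidedness, since neither a one-sided nor a two-sided reading of 3 SD gives P<0.001. The two-sided convention, and a guide that covers benefit and harm alike, make 0.0027 the relevant figure. Results with |z| from 3.00 to 3.29 are classified differently by the two forms.

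The consequence is modest. The choice of form moves the type I error per comparison by 0.0141 − 0.0114 = 0.0027 at a final level of 0.01, and by 0.0529 − 0.0510 = 0.0019 at 0.05. These figures assume looks at exactly 200 and 400 of 1000 patients, stopping at every crossing and no adjustment of the final test. Because the guide is advisory, they describe the boundary itself and do not predict what the committee would do. The error does not threaten the trial's conclusions, and the documents do not show which form was intended.

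**What to change.** Replace the double statement with one boundary and its sidedness, in the protocol or by reference to the committee's charter. Either of these is coherent:

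- two-sided P<0.001 (|z| at least 3.29); or
- 3 standard deviations (two-sided P<0.0027).

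The first fits better with the remark that the number of looks hardly matters, because it leaves the smaller excess over the nominal level. Its only cost is a slightly stricter guide for early stopping. With the second, that remark is less well supported against the 0.01 level used for sizing. Neither choice changes the sample size, the timing of the looks or the conduct of the trial.
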